## Abstract

**Background:**

Various methods are currently used for the induction of labor. Nevertheless, the most effective method with the fewest side effects remains to be established. Misoprostol, administered vaginally, has been routinely used for this purpose; however, other forms of administration are being proposed, including the use of sublingual tablets. No studies have yet compared the effectiveness and safety of 12.5-μg misoprostol administered sublingually compared to a 25-μg vaginal dose of the drug for the induction of labor.

**Methods:**

A triple-blind, multicenter, placebo-controlled, randomized clinical trial will be conducted in Brazil at the *Instituto de Medicina Integral [name]* and at the Assis Chateaubriand Maternity Teaching Hospital of the Federal University of Ceará. A total of 140 patients with full-term pregnancies, a live fetus, a Bishop score ≤ 6 and a recommendation of induction of labor will be randomized to one of two groups. One group will receive 12.5-μg sublingual tablets of misoprostol and placebo vaginal tablets, while the other group will receive placebo sublingual tablets and vaginal tablets containing 25 μg of misoprostol. The principal endpoint is the rate of tachysystole. The secondary endpoints are vaginal delivery within 24 h of induction, uterine hyperstimulation, Cesarean section, severe neonatal morbidity or perinatal death, severe maternal morbidity or maternal death, and maternal preference regarding the route of administration of the drug. Student’s t-test, and the chi-square test of association or Fisher’s exact test, as appropriate, will be used in the data analysis. Risk ratios and their respective 95% confidence intervals will be calculated.

**Discussion:**

Misoprostol has been identified as a safe, inexpensive, easily administered option for the induction of labor, with satisfactory results. An experimental study has shown that misoprostol administered sublingually at a dose of 25 μg appears to be effective and is associated with greater maternal satisfaction when labor is induced in women with an unfavorable cervix. Nevertheless, the rate of tachysystole remains high; therefore, further studies are required to determine the ideal dose and the ideal interval of time between doses.

**Trial registration:**

ClinicalTrial.gov, NCT01406392.

## Plain summary

Various methods are currently used for the induction of labor. Nevertheless, the most effective method with the fewest side effects remains to be established. Misoprostol, administered vaginally, has been routinely used for this purpose; however, other forms of administration are being proposed, including the use of sublingual tablets. No studies have yet compared the effectiveness and safety of 12.5-μg misoprostol administered sublingually compared to a 25-μg vaginal dose of the drug for the induction of labor. A triple-blind, multicenter, placebo-controlled, randomized clinical trial will be conducted in Brazil at the *Instituto de Medicina Integral [name]* and at the Assis Chateaubriand Maternity Teaching Hospital of the Federal University of Ceará. A total of 140 patients with full-term pregnancies, a live fetus, a Bishop score ≤ 6 and a recommendation of induction of labor will be randomized to one of two groups. One group will receive 12.5-μg sublingual tablets of misoprostol and placebo vaginal tablets, while the other group will receive placebo sublingual tablets and vaginal tablets containing 25 μg of misoprostol. The principal endpoint is the rate of tachysystole.

## Background

Induction of labor refers to any procedure used to stimulate uterine contraction before it occurs spontaneously [1]. When the continuation of pregnancy represents a risk to the mother and/or the fetus that is greater than the risk of interrupting the pregnancy, labor induction is an option to allow vaginal delivery to occur [2].

Misoprostol is a synthetic analog of prostaglandin E1 that acts on the cervix and on the uterine smooth muscle, facilitating cervical dilatation and promoting uterine contractions [3]. The first time misoprostol was used for labor induction involving a live fetus was in 1991, and the drug was administered vaginally [4]. Since then, various studies have been conducted using different dosage regimens and progressively lower doses. In addition, some studies have compared misoprostol with other methods of labor induction, while others have compared different routes of administration [5–8].

Currently, the most commonly used and recommended routes of administration of misoprostol for labor induction in routine practice are the vaginal and oral routes at a dose of 25 μg [6, 7, 9]; however, the sublingual and buccal routes have also been proposed [5, 8].

The administration of misoprostol by the sublingual route was proposed as a means of reducing the number of vaginal examinations, thus providing patients with greater comfort and possibly also reducing rates of maternal and fetal infection [10]. In addition, evaluation of the pharmacokinetics of the drug showed a higher peak of plasma concentration in pregnant women receiving misoprostol by the sublingual route compared to oral or vaginal administration or to vaginal administration with the addition of water. The bioavailability of the drug is also greater with the use of the sublingual route of administration [3]. On the other hand, plasma levels are maintained over a longer period of time when the vaginal route is used [3].

In a systematic review that included five clinical trials comparing misoprostol administered sublingually and vaginally, no statistically significant difference was found between the two groups in relation to the rate of vaginal deliveries within the first 24 h, to the rate of uterine hyperstimulation or to the Cesarean section rate. There was, however, a greater risk of tachysystole in the sublingual misoprostol group [10]. Those authors also suggested that this effect was dose-dependent; i.e. the higher the dose of misoprostol, the greater the risk of tachysystole. In that study, the lowest dose used was 25 μg [10]. Therefore, those authors concluded that new studies would have to be conducted to determine the lowest effective dose with the fewest side effects [10].

This study was proposed with the objective of comparing the effectiveness and safety of the sublingual administration of 12.5 μg of misoprostol (low dose) with the vaginal administration of 25 μg of misoprostol (standard recommended dose) for the induction of labor involving a live, full-term fetus.

## Methods/design

### Setting and recruitment

The study will be developed at the *Instituto de Medicina Integral [name]* and at the Assis Chateaubriand Maternity Teaching Hospital of the Federal University of Ceará, all of which are situated in northeastern Brazil. These institutions provide integrated women’s healthcare that encompasses primary, secondary and tertiary healthcare. They operate as university teaching hospitals, receiving students from the Medical and Nursing Schools, and also have a medical residency program in Obstetrics and Gynecology and postgraduate programs. In each institute, around 400–450 births take place every month, with induction of labor being indicated in approximately 10–20% of cases.

### Participant selection

The attending obstetrician will identify possible candidates for the study. An ultrasound scan will be performed and a checklist will be completed to evaluate whether the candidate fulfills the eligibility criteria for inclusion in the study. If the woman is eligible, she will then be provided with explanations regarding the reason for conducting the study and its importance.

All the patients included in the study will be provided with information regarding the objectives and possible consequences of their participation. If they voluntarily agree to participate, they will then be asked to sign an informed consent form and will be referred for antepartum care under the responsibility of the investigators and the duty obstetricians.

### Study design

A multicenter, triple-blind, randomized, controlled clinical trial will be conducted.

### Inclusion criteria

Gestational age ≥ 37 weeks; live fetus; cephalic vertex presentation; Bishop score ≤ 6; and the presence of clinically satisfactory fetal vitality.

### Exclusion criteria

Ultrasound-estimated fetal weight ≥ 4000 g; amniotic fluid index < 5; previous Cesarean section; previous uterine scar from a myomectomy or other uterine surgery; genital bleeding of unexplained origin; fetal anomalies; tumors, malformations and/or ulcerations in the vulvoperineal region and birth canal that could be harmful to the mother and/or fetus during labor; and chorioamnionitis.

### Sample size

Predicting a frequency of tachysystole of 6,7% % in the 12.5-μg sublingual misoprostol group (pilot study) and of 13.2% in the 25-μg vaginal misoprostol group [7], for a 95% confidence interval and a power of 80%, 70 women would have to be recruited to each group.

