## Discussion

The technological progress achieved in modern obstetrics permits effective techniques to be used to diagnose maternal and fetal situations requiring early elective delivery. One of the principal limiting factors to this process is the condition of unfavorable cervix, which hampers induction of labor, consequently contributing towards increasing Cesarean section rates.

Misoprostol has been identified as a safe, inexpensive, easily administered option for the induction of labor, with satisfactory results. An experimental study showed that sublingual misoprostol at a dose of 25 μg appears to be effective and is associated with greater maternal satisfaction when used to induce labor in women with an unfavorable cervix. Nevertheless, the rate of tachysystole remains high; therefore, further studies need to be conducted to determine the dose and the ideal time interval between doses to minimize the side effects. The only clinical trial conducted using a 12.5-μg dose of misoprostol administered sublingually, a non-randomized open study with no control group, reported that labor was successfully triggered in 90% of cases, with vaginal deliveries occurring in 60% of the women, and a rate of 47% of vaginal deliveries within 24 h [11]. When the frequency of tachysystole found in that study is compared with others in which misoprostol was used vaginally at a dose of 25 μg, a similar frequency of between 4.3 and 6.6% is found [10]. The systematic review available in the Cochrane Library suggests a global rate of uterine hyperstimulation with no changes in fetal heart rate of 11% with 25 μg of misoprostol, even higher than that found in an earlier review [7]. Nevertheless, these results are based on a single clinical trial with no control group, thus rendering comparisons difficult.

We believe that with this low dose of misoprostol administered sublingually the frequency of tachysystole or uterine hyperstimulation may be lower than that found with the habitual 25 μg dose of misoprostol administered vaginally, since it was suggested in a systematic review that the occurrence of tachysystole with misoprostol is probably dose-dependent [11].

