This will be the first randomized, controlled clinical trial to compare the effectiveness and safety of misoprostol at a dose of 12.5 μg administered sublingually with the currently standard 25 μg dose administered vaginally every six hours to induce labor in pregnant women with a full-term live fetus. Expectations are that the present study will clarify whether the rate of tachysystole during labor induction is lower in the sublingual group. On the other hand, no differences between the groups are expected with respect to uterine rupture, need for analgesia during labor, need for operative vaginal delivery or the rate of maternal death.

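### The 13.2% control rate behind the planned effect and the stated 80% power is not reconciled with the 4.3–6.6% that the Discussion gives for the same dose and route

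*Protocol article*

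**What the plan says.** The Sample size section gives the sublingual assumption as "Predicting a frequency of tachysystole of 6,7% % in the 12.5-μg sublingual misoprostol group (pilot study") and the vaginal one as a rate "of 13.2% in the 25-μg vaginal misoprostol group [7"]. It continues "for a 95% confidence interval and a power of 80"% and concludes that "70 women would have to be recruited to each group". Tachysystole is the primary endpoint.

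The Discussion describes an uncontrolled, open study of 12.5 μg sublingual misoprostol. It compares the tachysystole frequency in that study with studies of 25 μg given vaginally, and says that "a similar frequency of between 4.3 and 6.6% is found [10"]. It then cites this from a review: "uterine hyperstimulation with no changes in fetal heart rate of 11% with 25 μg of misoprostol, even higher than that found in an earlier review", which is a differently labelled outcome. It warns that comparison is difficult because the data come from one trial without a control group.

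It nevertheless expects a lower frequency with the sublingual dose, on the ground that the effect is probably dose-dependent, and expects the trial to "clarify whether the rate of tachysystole during labor induction is lower in the sublingual group".

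**The concern.** Two sections give different rates for the same outcome, drug, dose and route. The planning rate of 13.2% is two to three times the Discussion's range (13.2/6.6 = 2.0; 13.2/4.3 = 3.1). The figure 13.2% appears nowhere else in the article, and nothing says why it was preferred.

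The choice matters because the control rate fixes the planned effect. Against 6.7%, a control rate of 13.2% means that tachysystole is roughly halved. A control rate within 4.3–6.6% leaves no reduction to detect. A reader who sees only the 80% cannot tell how strongly that figure depends on one literature value, or that the article quotes lower ones.

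**Working it through.** **Inputs.** Sublingual rate p₁ = 6.7%, control rate p₂ = 13.2%, 95% confidence, 80% power and 70 per group, all from the Sample size section. Alternative control rates of 4.3%, 6.6% and 11% come from the Discussion. Sidedness is not stated; two-sided 5% is assumed.

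**Step 1: the plan's own figure.** With the usual pooled-variance formula,

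n = [z₀.₉₇₅ √(2p̄(1−p̄)) + z₀.₈₀ √(p₁(1−p₁) + p₂(1−p₂))]² / (p₂ − p₁)²

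- p̄ = (0.067 + 0.132)/2 = 0.0995
- √(2 × 0.0995 × 0.9005) = 0.4233
- √(0.067 × 0.933 + 0.132 × 0.868) = 0.4208
- n = (1.960 × 0.4233 + 0.8416 × 0.4208)² / 0.065² = 1.1839² / 0.004225 ≈ 332 per group

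The stated 70 is not reproduced. One-sided testing gives 262, the unpooled formula 329 (one-sided 260), the arcsine formula 325 (one-sided 256), and a one-sample test against a fixed 13.2% gives 181.

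In the other direction, power at n = 70 is Φ[(0.065 × √70 − 1.960 × 0.4233)/0.4208] = Φ(−0.68) ≈ 25% two-sided, or 36% one-sided. With 6.7% in the sublingual arm, 70 per group reaches 80% power only if the control rate is about 23.5%.

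**Step 2: vary the control rate.** The two binomial distributions were enumerated exactly with 70 per group, an uncorrected chi-square test and |z| > 1.96, counting only significant results that favour sublingual. Reduction is control minus sublingual; the risk ratio is sublingual over control.

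| Control rate | Where stated | Reduction (points) | Risk ratio | Chance of significance favouring sublingual |
|---|---|---|---|---|
| 13.2% | Sample size | 6.5 | 0.51 | 25% |
| 11% | Discussion (other outcome label) | 4.3 | 0.61 | 14% |
| 6.6% | Discussion | −0.1 | 1.02 | 2.4% |
| 4.3% | Discussion | −2.4 | 1.56 | 0.5% |

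At 4.3% the chance of a significant result in the opposite direction is 8.6%. With Fisher's exact test, which the Analysis section also allows, the chances are lower: about 17% at 13.2%, 8% at 11% and 0.9% at 6.6%.

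**Step 3: separate the two effects.** The fall from 80% to 25% occurs at the plan's own rates and is a fault in the sample-size arithmetic. Only the further fall, from 25% to 14%, 2.4% or 0.5%, comes from the control rate. Correcting the arithmetic alone would not settle the matter: at 11% the same formula asks for about 684 per group, and at 4.3–6.6% no sample size gives power for a reduction, because none is expected.

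**The case against.** Choosing one published rate among several is a planning judgement, and the article discloses the lower figures together with their limits. Several points on this side stand.

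- **The 11% is weak evidence.** It is labelled hyperstimulation without fetal heart rate changes, and the article lists hyperstimulation as an endpoint separate from tachysystole. It also leaves a 4.3-point reduction.
- **The citation proves nothing.** A reader might infer that reference [7] cannot have yielded 13.2%, because the Discussion ties [7] either to the 11% or to something lower. That assumes the source reports a single rate. A review can report several outcomes, and this one is not at hand.
- **The hypothesis does not rest on 13.2%.** Its stated ground is dose-dependence. The 13.2% sets only the size of the planned effect.
- **The comparison behind 4.3–6.6% crosses studies.** The 12.5 μg data come from an uncontrolled study. That this study is also the pilot behind the 6.7% is an inference.
- **The stated objective is a comparison** of effectiveness and safety, so a null result would still inform it. The Analysis section already plans risk ratios with 95% confidence intervals.

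What does not fall away is the conflict itself. The 4.3–6.6% is given for tachysystole with 25 μg vaginally, the very quantity set at 13.2%. Dose-dependence supports a direction, not a magnitude. Nor is this a detail that an article may leave to a fuller document: both figures are printed and they disagree.

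**Conclusion.** The point holds as an unreconciled inconsistency in the planned effect size and stated power. The control rate of 13.2% stands against 4.3–6.6% for the same outcome, dose and route. Over the rates the article cites, the expected reduction runs from 6.5 points to −2.4 points, and the chance of a significant result favouring sublingual from about 25% to 0.5%. None of these approaches 80%.

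These figures assume 6.7% in the sublingual arm, 70 analysed per group, and an uncorrected chi-square test at two-sided 5%.

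A reader might go further and conclude that 13.2% is wrong, or that a null result is the expected outcome. The documents do not support either. The sources cannot be checked here, and the low range rests on a comparison that the authors themselves qualify.

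**What to change.** Reconcile the Sample size section with the Discussion: say why 13.2% was chosen as the control rate for tachysystole when 4.3–6.6% is quoted for the same regimen. Replace the single claim of 80% power with a short table of the expected difference and the power at the planned 140 women, for control rates from 4.3% to 13.2%. State the test and its sidedness with the table.

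Changing the control rate alone will not repair the calculation, since 70 per group does not follow from 6.7% and 13.2% either. The table must therefore be computed afresh.

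The cost is a few sentences and one table, with no additional patients or data. The downside is that the stated power becomes much less favourable.

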### Randomization and preparation of the medications

The Random Allocation software program, version 1.0.0 (Isfahan, Iran) will be used to randomize participants in the study to labor induction with sublingual or vaginal misoprostol, using the letters A and B, with no prior knowledge or indication of what each letter means. The meaning of the letters will be defined in a random draw conducted by the pharmacist. Neither the investigators nor the statistician will have access to that information. The pharmacist responsible for preparing the medication will place the sublingual misoprostol tablets + the placebo vaginal tablets or the placebo sublingual tablets + the misoprostol vaginal tablets in standardized boxes in accordance with the randomization list. Everyone else in the study (investigators, statistician and participants) will remain blinded to this information until data analysis is complete.

Identical boxes will be prepared and numbered sequentially from 1 to 140 in accordance with the randomization table. Each box will contain a set of eight vaginal tablets (placebo or 25 μg of misoprostol) and eight sublingual tablets (placebo or 12.5 μg of misoprostol), thus guaranteeing the triple-blind design of the study, since neither the investigators nor the pregnant women nor the statistician will be aware of the contents of the boxes.

The vaginal and sublingual placebo and misoprostol tablets will be produced by the pharmaceutical company *Hebron Indústrias Químicas e Farmacêuticas*. The vaginal tablets of misoprostol consist of misoprostol, together with lactose, microcrystalline cellulose, aerosil, explocel, sorbitol and talc, and are sold commercially under the brand name Prostokos^®^ (25 μg). For the purposes of the present study, the aforementioned pharmaceutical company will prepare 12.5-μg tablets of misoprostol for sublingual use. The placebo vaginal and sublingual tablets will be identical in shape, size, color, smell, taste and weight to those containing the active drug prepared specifically for the study, and will be stored in indistinguishable cardboard boxes.

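### At the stated tachysystole rates, 70 women per group give about 25% power, not 80%; the stated assumptions need about 332 per group

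*Protocol article*

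**What the plan says.** The Sample size section of the protocol article gives every input and a result. The sublingual rate is introduced as "Predicting a frequency of tachysystole of 6,7% % in the 12.5-μg sublingual misoprostol group (pilot study", the doubled percent sign being as printed. The comparator rate is "of 13.2% in the 25-μg vaginal misoprostol group", taken from a cited review. The conclusion is "for a 95% confidence interval and a power of 80%, 70 women would have to be recruited to each group".

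The resulting total of 140 appears in the Abstract and the Plain summary. It also fixes the drug supply: the boxes are "numbered sequentially from 1 to 140". Tachysystole is the only primary endpoint. The Analysis section names the chi-square test or Fisher's exact test, with risk ratios and 95% confidence intervals. The aim is superiority, as the Discussion says: "Expectations are that the present study will clarify whether the rate of tachysystole during labor induction is lower in the sublingual group". No non-inferiority margin or one-sided test is given.

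**The concern.** Separating 6.7% from 13.2% is a difference of 6.5 percentage points between two uncommon event rates. With 70 women per group, these rates predict about 4.7 and 9.2 events. A gap of four or five events between arms is too small for a two-sided 5% test to detect reliably, so a claim of 80% power is implausible on its face.

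The primary endpoint is a safety outcome. If the true power is far below 80%, the most likely result is a non-significant comparison even when the low sublingual dose halves the risk as the investigators hope. A reader who trusts the printed 80% could take that result as good evidence against a difference, when the trial had little chance of showing one.

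**Working it through.** **Inputs**
- Sublingual rate p1 = 0.067, vaginal rate p2 = 0.132, power 80%, 70 per group: Sample size section.
- Significance level 5%, read from the 95% confidence level. Two-sided is the usual reading; the article does not state the sidedness, so one-sided is also tried.
- Equal allocation follows from 70 per group and 140 in total.

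**Trying to reproduce the 70**

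Pooled-variance formula, with p̄ = (0.067 + 0.132)/2 = 0.0995:

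n = [1.960·√(2p̄(1−p̄)) + 0.842·√(p1(1−p1) + p2(1−p2))]² / (p2−p1)²

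- √(2 × 0.0995 × 0.9005) = 0.4233; × 1.960 = 0.8297
- √(0.0625 + 0.1146) = 0.4208; × 0.842 = 0.3542
- n = (0.8297 + 0.3542)² / 0.065² = 331.7, so **332 per group, 664 in total**

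Other versions:

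| Method | n per group |
|---|---|
| Two-sided 5%, unpooled variance | 329 |
| Two-sided 5%, arcsine | 325 |
| Two-sided 5%, continuity-corrected | 362 |
| One-sided 5%, pooled | 262 |
| One-sided 5%, continuity-corrected | 292 |
| One-sided 20%, pooled | 120 |

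None comes near 70. The stated number is too small by a factor of 332/70 = 4.7.

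**Power with 70 per group at the planning rates**

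Normal approximation: (0.065 × √70 − 0.8297) / 0.4208 = (0.5438 − 0.8297) / 0.4208 = −0.68, so power = Φ(−0.68) = 24.8%.

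Exact enumeration over both binomial distributions, two-sided 5%:
- uncorrected chi-square: 25.1%
- Fisher's exact test: 16.9%

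One-sided 5%: 35.9% by the normal approximation, 27.6% by exact Fisher.

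**What 70 per group can detect**

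Holding p1 at 6.7% and solving the pooled formula for 80% power at n = 70 gives p2 of about 23.5%. The article gives no such rate.

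**What the result would look like**

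Expected events are 70 × 0.067 = 4.69 and 70 × 0.132 = 9.24. The risk ratio is 0.067/0.132 = 0.51. The standard error of its logarithm is √(1/4.69 − 1/70 + 1/9.24 − 1/70) = 0.541, so the 95% confidence interval is about 0.18 to 1.47. With whole counts of 5 and 9 it is 0.56 (0.20 to 1.57). Either interval covers both a large benefit and a material harm.

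**The case against.** The best counter-argument is that a rate may be misprinted and the sample size may be right. The sublingual rate is visibly mis-set, and a vaginal rate near 23.5% would fit 70 per group. The article shows only that rates, power and sample size cannot all hold, not which one is wrong. This part stands, and it means that the 25% and the 332 are conditional on the printed rates.

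It does not rescue the 70. Nothing in the article supports a vaginal rate near 23.5%, and the Discussion points the other way. It cites 4.3 to 6.6% in earlier vaginal 25-μg studies, and 11% from a systematic review for hyperstimulation without heart-rate changes, which may be defined differently. At 6.7% versus 11% the same formula needs about 684 per group, and power at 70 per group is about 15%. At 6.6% there would be essentially no difference to detect.

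A second objection is that risk ratios with 95% confidence intervals are already planned and that the article nowhere says a null result will be called similarity. That is true, so the misreading is a risk and not something the authors have committed to. But the printed 80% invites it.

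A condensed article is no defence either. All inputs and the result are printed, so the fault is a false statement and not an omission.

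**Conclusion.** The sample size statement is wrong as printed. At 6.7% versus 13.2%, two-sided 5% and 80% power, about 332 women per group are needed. The planned 70 give about 25% power by chi-square and about 17% by Fisher's test. If the printed rates are true, about three trials in four would be non-significant on the primary endpoint, and more if Fisher's test is used.

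These figures assume that the printed rates are the intended ones, equal allocation and no loss of participants. The conclusion does not depend on the formula or the sidedness: one-sided testing still needs 262 per group. This must be corrected, because it is the stated design basis of the only primary endpoint.

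**What to change.** Correct the Sample size section as follows.

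1. Confirm both planning rates and their sources, and reconcile the vaginal rate with the lower figures in the Discussion.
2. If 6.7% and 13.2% stand, state that 80% power at two-sided 5% needs about 332 per group (664 in total). State also that 70 per group give about 25% power, and reach 80% only for a contrast such as 6.7% versus about 23.5%.
3. State that the primary result will be read as an estimate with its 95% confidence interval, and that a non-significant result will not be reported as similar tachysystole rates.
4. Temper the Discussion's expectation that the trial will settle the question.

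The cost is wording and a less favourable stated power.

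Extending recruitment is a separate decision for the sponsor. The Setting section implies 2 × 400–450 births × 10–20%, or about 80 to 180 indicated inductions a month across both sites, before exclusions and consent. The planned pace is much slower: 140 women over August 2015 to July 2018 is about 4 a month (140/36), at which 664 women would take about 14 years.
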